### Data monitoring

In keeping with previous similar investigations [24], no formal Data Monitoring Committee has been created given the relatively short time span of follow-up, and minimal clinical risks. However, an interim assessment will be performed once recruitment is 50% complete. If at this point the difference in FTMH closure rates between groups crosses the 95% confidence interval of the clinically significant noninferiority margin of 15% as determined by previous investigations assessing FTMH closure [7, 24], the study will be terminated.

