### Objectives

Our primary objective will be focused on assessing feasibility. Feasibility will be assessed by measuring the recruitment rate, retention rate, and completion rate at 3 months following surgical repair as well as the recruitment time.

Our secondary outcomes will include a) macular hole closure rate at 3 months following surgery; two independent readers, masked to treatment allocation, will independently grade the outcome in each instance as closed, or open. Outcomes classified as open will be further divided into open and flat (without a cuff of subretinal fluid), or open and elevated (with a cuff of subretinal fluid). b) best-recorded visual acuity at 3 months post-surgery, c) compliance with FDP as assessed utilizing self-administered questionnaires four times per day during the duration of FDP, d) patient self-administered vision-specific validated quality of life measure, the 25-item National Eye Institute Visual Function Questionnaire (NEI VFQ-25) and a validated quality of life measure, the Quality of Life Scale (QOLS), and e) complication rates (endophthalmitis, retinal detachment, vitreous hemorrhage) as assessed by a masked physician.

The interpretation of findings will be: a) the full-scale trial is feasible with no changes to the protocol; b) the full-scale trial is feasible with small changes to the protocol; c) the full-scale trial is infeasible. The study will be considered feasible if the retention and completion rates are > 80% of randomized patients. The study will be considered feasible with small changes if either the retention or completion rate is <80% of randomized patients and the study will be considered infeasible if the completion and retention rates are <80% of randomized patients.

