### Sample size

The primary outcome of this investigation is to assess feasibility, as such, a power calculation to determine the sample size was not performed [15, 19, 20]. A literature review was undertaken to help inform the optimal sample size; no consensus was found with recommendations ranging from 24 to 50 described in the literature [21–23]. A previous RCT evaluating different positioning following PPV for FTMHs experienced a 10.2% attrition and thus we similarly estimate a 10% attrition rate in this investigation [24]. As such accounting for this attrition rate, utilizing a sample size of 40 patients, we will be able to estimate an 80% retention and completion rate to within a 95% confidence interval of +/-12.4% and a 33% recruitment rate to within a 95% confidence interval of +/- 14.6% [23]. We estimate based on previous rates of FTMH at our institution that there will be 3 new eligible patients each week. Previous studies at our institution have experienced a recruitment rate of 25%. Thus, we estimate that it will take approximately 53 weeks to achieve our target sample size.

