### Randomization and masking

Patients will be randomized 1:1 to the 3-day FDP or 7-day FDP groups utilizing permuted block randomization with blocks of 4, 6, and 8. Sequence generation will be performed in R (version 4.3.1, Vienna, Austria) by a research team member with experience generating lists for RCTs. The list will subsequently be uploaded to the online secure research platform Research Electronic Data Capture (REDCap) and allocation concealment will be maintained utilizing REDCap. Randomization will be performed immediately following completion of the surgical case and the surgeon will be immediately made aware of the patient’s allocation. At this point, the surgeon will inform the patient in the recovery room regarding their treatment allocation. Allocation concealment will be maintained utilizing REDCap. The randomization list will be made available to the remaining study team following the completion of the study.

All staff performing VA assessments and obtaining OCT images will be masked to treatment allocation. OCT grading of FTMH closure will be performed by two masked readers and disagreements will be resolved by a third masked reader. The participants themselves and the clinical teams managing their care will be unmasked.

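### The interim stopping rule refers to a confidence interval of a fixed margin, so it cannot be applied as written, and its confidence-interval readings behave badly at about 10 patients per arm

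*Protocol article*

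**What the plan says.** All places are in the protocol article.

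- **Data monitoring.** There is no formal monitoring committee, but "an interim assessment will be performed once recruitment is 50% complete". If at that point "the difference in FTMH closure rates between groups crosses the 95% confidence interval of the clinically significant noninferiority margin of 15" per cent, then "the study will be terminated". No other outcome of the look is described.
- **Objectives.** The closure endpoint is "macular hole closure rate at 3 months following surgery".
- **Data collection methods.** OCT is scheduled before surgery and at 1 and 3 months after it.
- **Sample size.** The plan is described as "utilizing a sample size of 40 patients". Expected accrual is 3 eligible patients a week with a 25% recruitment rate, giving about 53 weeks.
- **Randomization and masking.** "Patients will be randomized 1:1 to the 3-day FDP or 7-day FDP groups", so 20 recruits give about 10 per arm.

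**The concern.** The rule compares an observed difference with the confidence interval of a constant, and no such interval exists. Whoever runs the look must guess what was meant. The natural guesses lead to opposite decisions on the same data.

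The trigger is also tied to recruitment, while closure is defined at 3 months. Many of the patients counted at the trigger will not yet have the outcome.

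This is the only stated rule that can end the pilot. A chance stop at 20 patients would leave recruitment time unmeasured, because it is defined as the days needed to recruit 40. It would also widen the half-width for an 80% retention rate from the stated 12.4 points to 1.96 × √(0.8 × 0.2 / 20) = 17.5 points. A rule that hardly ever fires would give participants little protection from a real loss of closure.

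**Working it through.** **Inputs from the article:** 40 patients; 1:1 allocation; look at 50% of recruitment (20 patients, about 10 per arm); margin 15 points; 95% level; 3 eligible patients a week; 25% recruited; closure at 3 months (13 weeks).

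**Assumed:** the article gives no closure rate, so 85%, 90% and 95% are used. Differences are 3-day minus 7-day closure, so harm from shorter positioning is negative.

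**1. Accrual.** 3 × 0.25 = 0.75 patients a week, and 40 / 0.75 = 53.3 weeks, which reproduces the stated 53.

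**2. Patients without 3-month closure at the trigger.** The 20th patient arrives at 20 / 0.75 = 26.7 weeks.
- Planned rate: 0.75 × 13 = 9.75 of 20 (49%).
- Calendar dates in Study timeline and status (1 December 2023 to 31 December 2024, about 0.71 a week): 9.2 of 20 (46%).
- Planned rate, with surgery assumed 2 weeks after enrolment: 0.75 × 15 = 11.25 of 20 (56%).
- If the look instead waits for all 20, about 20 + 9.75 ≈ 30 of the 40 are already recruited.

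The planned 10% attrition would reduce the interim data further and is not applied here.

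**3. Interval width at 10 per arm.**
- 9/10 v 9/10, Wald: 1.96 × √(2 × 0.9 × 0.1 / 10) = ±26.3 points. Newcombe gives ±31.5.
- 10/10 v 10/10, Newcombe: the Wilson lower limit is 10 / (10 + 1.96²) = 0.722, so the interval is ±27.8 points. Wald collapses to zero width.

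**4. Stopping probabilities.** These come from exact enumeration: P(stop) = Σ b(x; 10, p3) × b(y; 10, p7) over all (x, y) that meet the rule, where b is the binomial probability.

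*Reading A: stop if the 95% interval reaches below -15 points. No true difference.*

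| Closure, both arms | Newcombe | Wald |
|---|---|---|
| 85% | 89% | 74% |
| 90% | 90% | 62% |
| 95% | 95% | 40% |

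With Newcombe limits, even 10/10 closed in the 3-day arm against 9/10 in the 7-day arm (-18.9 to +40.4) would end the study.

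*Reading B: stop only if the whole interval lies beyond -15 points. 7-day closure 90%.*

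| True deficit | Newcombe | Wald |
|---|---|---|
| 15 points | 0.8% | 2.9% |
| 20 points | 2.1% | 5.7% |
| 30 points | 8.2% | 15.2% |
| 40 points | 20.9% | 29.5% |

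At 5/10 v 10/10 closed, Newcombe (-76.3 to -11.7) continues and Wald (-81.0 to -19.0) stops.

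*Reading C: stop if the observed 3-day deficit is at least 15 points.* With 10 per arm this means at least 2 fewer closures. At 90% 7-day closure it stops 12% of trials with no true difference, 50% at a 15-point deficit, 61% at 20 and 80% at 30.

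**5. If only patients with 3-month data are used (about 5 per arm).** At 90% closure, Reading A stops 95% (Newcombe) or 60% (Wald) of trials with no true difference. At a 20-point deficit, Reading B stops 2% (Newcombe) or 10% (Wald).

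**The case against.** The best defence is that a journal article condenses a fuller protocol, so the interval method, data cut and analysis set may be fixed elsewhere. That stands for those details, and their absence alone would not be a finding. It does not rescue the sentence, which states a comparison that does not exist and attaches mandatory termination to it.

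A reader might infer more than the article supports:

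- **That every reading either stops most trials or almost never stops.** Reading C does neither (12% and 50%), and Reading A with Wald limits at 95% closure stops 40%. The extremes belong to the confidence-interval readings, and for deficits of 30 points or more, Reading B is better described as stopping few trials than almost none.
- **That the rule has no direction.** A noninferiority margin is one-sided by meaning, and 7 days is named as the control. The direction should be written down, but it can be inferred.
- **That a by-arm look contradicts the masking plan.** The article says "The randomization list will be made available to the remaining study team following the completion of the study", but comparing patients already randomised does not require release of the sequence. The surgeon learns each allocation at once, and the clinical teams are unmasked.
- **That this is the only safety protection.** A physician assesses complications at 1 week, 1 month and 3 months, and there are scheduled and discretionary visits. It is only the sole stated rule for ending the trial.

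The missing-outcome share is an expectation under planned accrual, and a 1-month OCT exists. The article does not say that the interim look uses it.

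**Conclusion.** The rule is wrong as written and should be replaced before it is used. The lack of any confidence interval for a margin needs no assumption. The stopping probabilities rest on about 10 per arm and on assumed closure rates. Under the reading where the interval need only reach below -15 points, 40 to 95% of trials with no true difference stop, depending on closure rate and interval method. Under the reading where the whole interval must lie beyond -15 points, 1 to 3% stop at a true 15-point deficit, 2 to 6% at 20 points and 8 to 15% at 30 points, with 7-day closure at 90%. Separately, about 46 to 56% of the first 20 patients are expected to lack 3-month closure at the trigger. Whether the pilot continues would depend on the reading adopted on the day.

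**What to change.** Replace the sentence with one evaluable, one-directional harm guideline (3-day arm worse) that states:

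- the statistic, for example a difference in counts of open holes, or a named interval for the difference;
- the closure time point used at the interim, for example the already scheduled 1-month OCT, or 3-month data with the look deferred;
- the analysis set and who runs the comparison;
- that failing to show noninferiority at the interim is not a reason to stop.

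Report its stopping probabilities under no difference and under 15- and 30-point deficits, over a range of closure rates and for unequal arm sizes. The sponsor should choose the threshold from those figures.

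The cost is a one-paragraph amendment with no new data collection. If the 1-month OCT is used, it stands in for 3-month closure at the interim only, and the article offers no evidence on how well it does so. If the look waits for 3-month data, about 30 of the 40 patients will already be recruited.

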## Discussion

There is a gap in the current literature evaluating the optimal duration of FDP following FTMH repair. This is evident by the heterogeneity in practice patterns, lack of clear guidelines, lack of biologic rationale, and imprecision in pooled estimates in meta-analysis on the topic [12]. Moreover, FDP can be disabling for patients; [12] patient values and preferences must be taken into consideration with the current evidence when making decisions in clinical practice [25]. There is a need for a large well-conducted randomized controlled trial evaluating key outcomes to surgeons and patients including patient-reported outcome measures.

Pilot trials are an underutilized method of assessing the feasibility of large, expensive full-scale studies and can greatly increase the likelihood of success as well as minimize potential sources of waste in the main trial [15, 16]. Moreover, a pilot trial will provide great insight into the resource and management requirements of the future larger-scale trial [15, 16].

The strengths of this protocol include the multiple measures introduced to limit potential sources of bias. Firstly, randomization will occur in permuted blocks of 4,6, and 8 to protect against selection bias. Individuals involved in identifying patients and obtaining consent will not be involved in the sequence generation of the randomization list. Additionally, a single highly experienced surgeon ([name]) will be performing PPV in both groups and will be masked to the patient’s treatment allocation at the time of surgery. While an element of bias is inevitable given that it will not be possible to blind patients to their allocation, we do not anticipate that this will affect our primary objectives of determining the feasibility of a larger-scale trial. Moreover, for the future main trial, the FTMH closure rate will be graded by two masked assessors and visual acuity will be assessed by a member of the research team masked to the patient’s treatment allocation. International experts in retinal diseases ranked FTMH closure rate and postoperative visual acuity as the two most important outcomes pertaining to FTMH repair [12]. Consequently, the proposed methodology ensures that all potential sources of bias pertaining to the assessment of these two outcomes are minimized. Lastly, analyses will be performed on an intention-to-treat basis to best preserve randomization and prognostic balance in study arms and minimize the type I error rate.

The limitations of the proposed investigation primarily pertain to the inherent limitations of pilot trials; namely, that the patient important research question is not answered with this investigation. However, pilot trials have repeatedly been demonstrated to facilitate a high-quality subsequent trial and we believe that this approach optimizes the chance of a successful rigorous definitive trial [15, 16, 26, 27].

In conclusion, this protocol outlines the detailed methodology for a pilot RCT that will determine the feasibility of a future larger-scale trial comparing 3 days to 7 days of FDP following FTMH repair. The main trial will help to answer a patient important question with significant clinical equipoise.
